### Outcome measures

#### Primary outcome

Quality of dying during the last 48 hours of life: the patient’s symptom frequency and symptom burden measured using the EOLD-SM and EOLD-CAD [26].

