**Methods and design:**

A cluster randomized controlled trial will be conducted. Ten hospitals with one or more acute geriatric wards will conduct a one-year baseline assessment during which care will be provided as usual. For each patient dying in the ward, a questionnaire will be filled in by a nurse, a physician and a family carer. At the end of the baseline assessment hospitals will be randomized to receive intervention (implementation of the Care Programme) or no intervention. Subsequently, the Care Programme will be implemented in the intervention hospitals over a six-month period. A one-year post-intervention assessment will be performed immediately after the baseline assessment in the control hospitals and after the implementation period in the intervention hospitals. Primary outcomes are symptom frequency and symptom burden of patients in the last 48 hours of life.

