### Measurement instruments

Primary and secondary outcomes will be measured retrospectively after each death on the ward using questionnaires to be filled out by three different respondent types: the nurse who was most closely involved in the care for the deceased patient, the physician who was most closely involved in the care for the deceased patient, and a family carer of the deceased patient. The nurse and family carer questionnaires contain validated measurement instruments, in addition to self-developed questions. The physician questionnaire only contains self-developed questions (Table 2). Regarding the validated measurement instruments, the nurse questionnaire contains: the End-of-Life in Dementia Scales Symptom Management (EOLD-SM) [26], the End-of-Life in Dementia Scales Comfort Assessment in Dying Management (EOLD-CAD) [26] and the Palliative care Outcome Scale (POS) [27].

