**Table 2 Tab2:** **Content of the three different questionnaires for nurses, physicians and family carers**

**Questionnaire**	**Questions**	**Scale**	**Primary and secondary outcomes**
**Nurse**	Used from a scale	EOLD-SM	Symptom frequency*
		EOLD-CAD	Symptom burden*
		POS	Quality of care
	Self-developed questions		Content of care, i.e. nursing interventions,
			Communication between clinical staff and patients and/or family carers of dying patients
			Communication among clinical staff
**Physician**	Self-developed questions		Content of care, i.e. goal of treatment, medical interventions, medication policy
			Communication among clinical staff
**Family carer**	Used from a scale	EOLD-SM	Symptom frequency*
		EOLD-CAD	Symptom burden*
		FPPFC	Communication between clinical staff and patients and/or family carers of dying patients
		EOLD-SWC	Quality of care
		PGD	Level of bereavement
	Self-developed questions		Communication between clinical staff and patients and/or family carers of dying patients

*primary outcome.

In the questionnaire for the family carer the following validated instruments are included: the EOLD-SM [26], the EOLD-CAD [26], the End-of-Life in Dementia Scales Satisfaction With Care (EOLD-SWC) [26], the Family Perception of Physician-Family Caregiver Communication (FPPFC) [28] and the Prolonged Grief Disorder (PGD) Scale [29]. All three questionnaires have been cognitively tested in face-to-face interviews with four nurses, four physicians and three family carers respectively, and were subsequently refined where needed.

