### Sample size calculation

The hypothesis of this cluster randomized trial is that there will be significant differences in symptom frequency and symptom burden between patients dying in the intervention group and those dying in the control group. Symptom frequency and symptom burden will be measured using the EOLD-SM and the EOLD-CAD. Because our primary outcome is a reduction in symptom frequency and symptom burden during the last 48 hours of life, we consider a total EOLD-CAD score of 3.2 (7.6%) as the minimum clinically important difference for implementing the Care Programme for the Last Days of Life [30]. A minimum increase of 3.2 in the intervention group compared to the control group corresponds with an effect size (EC) of about 0.55. A minimum change of 5% to 10% has been found to be clinically significant for symptom and quality-of-life analyses [31]. In order to calculate the sample size of this cluster trial two other elements are essential: the intra-cluster correlation coefficient and the average size of the cluster (number of cluster deaths). We estimate an intra-cluster correlation coefficient of between 0.02 and 0.05 [32] and a conservative average of 30 deaths per hospital per year based on observed mortality statistics, taking into consideration the non-included deceased patients. In Table 3 four ICC scenarios (from 0.02 to 0.05) intersect with three scenarios of average size of the cluster (from 20 to 40). This table reports different sample size scenarios necessary to detect an ES of 0.55 with alpha = 0.05 and a power of 80% conditional on the hypothesized levels of ICC (from 0.02 to 0.05) and average size of cluster (from 20 to 40).

**Table 3 Tab3:** **Total number of clusters required according to different average sizes of the clusters and ICC (ES = 0.55, alpha = 0.05, power = 0.80)**

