### Statistical analysis

All data collected through the three different questionnaires will be stored and collected in Ghent University Hospital using IBM SPSS Statistics. Data cleaning will be performed via SPSS syntax operations. All statistical tests will be done two-tailed with 95% confidence intervals. A p-value <0.05 will be considered statistically significant.

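### Two primary scales, both starred for two raters, are tested at an unadjusted 0.05, while the sample size covers one EOLD-CAD test with no rater named

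*Protocol article*

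**What the plan says.** - **Scales.** The Primary outcome section gives "symptom frequency and symptom burden measured using the EOLD-SM and EOLD-CAD". The abstract uses the plural: "Primary outcomes are symptom frequency and symptom burden of patients in the last 48 hours of life". The Multivariable analysis section also treats both scales as primary outcomes.
- **Raters.** Under Measurement instruments, "the nurse questionnaire contains: the End-of-Life in Dementia Scales Symptom Management (EOLD-SM) [26", followed by EOLD-CAD. For the family carer, "the following validated instruments are included: the EOLD-SM [26], the EOLD-CAD [26". Table 2 puts the primary-outcome asterisk on both scales for both raters, so four rows are starred.
- **Decision threshold.** The Statistical analysis section says "All statistical tests will be done two-tailed with 95% confidence intervals" and "A p-value <0.05 will be considered statistically significant". It sets no separate level for the primary outcomes.
- **Sample size.** One scale is used: "we consider a total EOLD-CAD score of 3.2 (7.6%) as the minimum clinically important difference". The calculation takes effect size 0.55, two-sided alpha 0.05 and power 80%. It arrives at six clusters of 30 per group at ICC 0.05. It names no rater and does not cover EOLD-SM.
- **How the outcomes combine.** The hypothesis in the Sample size section joins symptom frequency and symptom burden with *and*. The aim in the Multivariable analysis section is to find any differences on the two scales. Neither is worded as a rule for declaring success.

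**The concern.** The article fixes several primary measures, one flat threshold, and a power statement for a single test. These do not fit together on either natural reading. If one significant result is enough, the chance of a false claim exceeds the 5% attached to each test. If all must be significant, the chance of success when the programme works is below the power of a single test.

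The raters make this a practical matter. Nurses respond within a week of the death. Family carers are sent a form at six weeks, after separate consent. Their ratings could diverge. If one rater's result is positive and the other's is null, the article does not say what the trial has shown.

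**Working it through.** **Inputs from the article.** Effect size 0.55 (3.2 points, so an implied SD of 3.2/0.55 = 5.82), alpha 0.05 two-sided, power 0.80, m = 30 per cluster, ICC 0.05, k = 6 clusters per group. The abstract plans ten hospitals and the recruitment section 10 to 12, so k = 5 is also shown.

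**Assumptions not in the article.** The correlation r between test statistics is taken as 0.3 to 0.7, with 0.9 as an extreme. For joint power, EOLD-SM and the family carer scores are given the same effect size, ICC and 30 responses per hospital as EOLD-CAD. That is generous for family carer forms, which need separate consent and postal return.

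**Step 1: reproduce the article's figure.** Without clustering, n per group = 2 × ((1.960 + 0.842)/0.55)² = 51.9, so 52. The design effect is 1 + 29 × 0.05 = 2.45. Power comes from a noncentral t with 2(k − 1) degrees of freedom and noncentrality 0.55/√(2 × 2.45/(30k)).

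- k = 6: noncentrality 3.33, 10 df, power 85.1%.
- k = 5: noncentrality 3.04, 8 df, power 76.0%.

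Six per group is the smallest number that reaches 80%, so 12 clusters are needed, as stated. The same method matches all twelve cells of Table 3. The calculation is therefore for one test at 0.05.

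**Step 2: error rate if any one result suffices.** For q independent tests the rate is 1 − 0.95^q.

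- q = 2: 1 − 0.95² = 9.75%.
- q = 4: 1 − 0.95⁴ = 18.5%.

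For equally correlated t statistics with 8 df, by simulation:

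| r | any of two | any of four |
|---|---|---|
| 0.3 | about 9.6% | 17.7% |
| 0.5 | about 9% | 16.3% |
| 0.7 | about 8.6% | 13.9% |
| 0.9 | about 7% | about 10% |

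**Step 3: power if all must succeed.** Same simulation, with every test given the noncentrality from Step 1 and r from 0.3 to 0.7:

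| Hospitals | single test | both scales, one rater | all four |
|---|---|---|---|
| 12 | 85.1% | 74–77% | 58–69% |
| 10 | 76.0% | 60–65% | 41–54% |

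Part of the ten-hospital shortfall comes from having fewer clusters, since a single test there has only 76%. The comparison with the stated 80% belongs to the 12-hospital row. At r = 0.9 and 12 hospitals, the simulation puts both-scales power at about 80%.

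**The case against.** **The success rule may be in a document not shown.** A condensed article commonly leaves hierarchy and multiplicity to the full protocol or analysis plan, so their absence alone would not be a finding. That stands. The point rests instead on what the article states: two primary scales, both starred for two raters, one unadjusted threshold, and a power claim for one test. A reader might also infer that the choice of deciding outcome will be made after the data are seen. Nothing in the article shows that.

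**Four tests is an inference.** It is tempting to say that the trial has four primary tests and a false-positive rate of 14 to 19%. The count of four comes only from the asterisks in Table 2. That table lists questionnaire content, and the asterisk may mark the construct wherever it is collected. The Primary outcome heading is singular, and the Multivariable analysis section does not say that each rater's score is tested separately. The four-test figures are therefore a conditional upper case, and 14% is not a floor. The two-scale figure is the safer one to lead with.

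**With *and* as the rule, there is no inflation.** This is correct. The article also claims only 0.05 per test and never a 5% family-wise rate. The cost then moves to power. For two scales at 12 hospitals it is about 3 to 6 points below the stated 80%, and about 8 to 11 points below the 85% that a single test attains.

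**Conclusion.** The concern holds in a conditional form. The primary outcomes, the threshold and the sample size do not add up to one defined test of success.

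- **Any one suffices:** the false-positive rate is about 9 to 10% for two scales from one rater (7% at correlation 0.9). It is at most 18.5% for four tests, about 14 to 18% at correlations 0.3 to 0.7 and 10% at 0.9.
- **All must succeed:** the error rate is controlled. Joint power at 12 hospitals is about 74 to 77% for both scales and 58 to 69% for all four. At ten hospitals it is 60 to 65% and 41 to 54%.

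The rates for independent tests are exact. The others depend on the assumed correlations, and the power figures also on equal effects and full response for every measure. The ten-hospital figures should not be read as the cost of multiple endpoints alone. This should be fixed. It does not invalidate the design, because a prespecified rule cures it cheaply and may already exist in a document not shown.

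**What to change.** Before the data are analysed, name one primary endpoint: total EOLD-CAD, the scale used in the sample size, from one prespecified rater, tested at two-sided 0.05. Then test EOLD-SM and the other rater's two scores in a prespecified fixed sequence, each at 0.05 and only if the one before it succeeds. Report both raters side by side whatever the result. State the rater in the sample size section too.

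The article does not dictate the lead rater. The nurse is a reasonable choice, because nurse forms need no separate family carer consent and so best match 30 per hospital. The drawback is that ward nurses are trained in the programme, deliver it, and cannot be taken as blinded to it. The choice should be argued openly.

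The cost is wording in the primary outcome, sample size and analysis sections. An isolated positive result lower in the sequence could no longer be claimed as confirmatory. Splitting alpha would cost more. At ICC 0.05 and 30 per cluster, two tests at 0.025 need 14 clusters, and four at 0.0125 need 16, instead of 12. With 12 clusters, power per test would be 74.7% and 62.3% respectively.

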#### Secondary outcomes

the quality of care during the last three days of life as perceived by nurses, i.e. physical symptoms, emotional, psychological and spiritual/existential needs and provision of information and support measured using the POS [27]the quality of care during the last 48 hours of life as perceived by family carers, i.e. satisfaction with the care provided to the patient during the last 48 hours of life measured using the EOLD-SWC [26]the content of care during the last 48 hours of life, i.e. the goal of treatment, medical and nursing interventions, medication policythe communication among clinical staff, i.e. informing the family physician about the impending deaththe communication between clinical staff and patients and/or family carers, i.e. the perception of communication with the physician during the dying phase by family carers measured using the FPPFC [28]the level of bereavement of family carers after the death of the patient measured using the PGD scale [29].

#### Process evaluation

We will also evaluate the quality of the process of implementation in the intervention group. An evaluation tool was developed to measure the degree to which the Care Programme for the Last days of Life was implemented in each ward in compliance with the implementation guide. For each component of the Care Programme indicators were developed so that the implementation of each individual component as well as the entire implementation process could be documented and quantitatively evaluated. This evaluation tool has been developed and piloted in a phase 2 study ([name], [name], [name], [name], [name], [name]: Feasibility and preliminary effects of the Care Programme for the Last Days of Life in an older acute hospital population: mixed-methods study of the success of implementation and staff perceptions, in preparation).

### Measurement instruments

Primary and secondary outcomes will be measured retrospectively after each death on the ward using questionnaires to be filled out by three different respondent types: the nurse who was most closely involved in the care for the deceased patient, the physician who was most closely involved in the care for the deceased patient, and a family carer of the deceased patient. The nurse and family carer questionnaires contain validated measurement instruments, in addition to self-developed questions. The physician questionnaire only contains self-developed questions (Table 2). Regarding the validated measurement instruments, the nurse questionnaire contains: the End-of-Life in Dementia Scales Symptom Management (EOLD-SM) [26], the End-of-Life in Dementia Scales Comfort Assessment in Dying Management (EOLD-CAD) [26] and the Palliative care Outcome Scale (POS) [27].

**Table 2 Tab2:** **Content of the three different questionnaires for nurses, physicians and family carers**

**Questionnaire**	**Questions**	**Scale**	**Primary and secondary outcomes**
**Nurse**	Used from a scale	EOLD-SM	Symptom frequency*
		EOLD-CAD	Symptom burden*
		POS	Quality of care
	Self-developed questions		Content of care, i.e. nursing interventions,
			Communication between clinical staff and patients and/or family carers of dying patients
			Communication among clinical staff
**Physician**	Self-developed questions		Content of care, i.e. goal of treatment, medical interventions, medication policy
			Communication among clinical staff
**Family carer**	Used from a scale	EOLD-SM	Symptom frequency*
		EOLD-CAD	Symptom burden*
		FPPFC	Communication between clinical staff and patients and/or family carers of dying patients
		EOLD-SWC	Quality of care
		PGD	Level of bereavement
	Self-developed questions		Communication between clinical staff and patients and/or family carers of dying patients

*primary outcome.

In the questionnaire for the family carer the following validated instruments are included: the EOLD-SM [26], the EOLD-CAD [26], the End-of-Life in Dementia Scales Satisfaction With Care (EOLD-SWC) [26], the Family Perception of Physician-Family Caregiver Communication (FPPFC) [28] and the Prolonged Grief Disorder (PGD) Scale [29]. All three questionnaires have been cognitively tested in face-to-face interviews with four nurses, four physicians and three family carers respectively, and were subsequently refined where needed.

### Data collection

During the baseline and post-intervention assessment, questionnaires will be filled in for all patients who died in the participating geriatric hospital wards and who met the inclusion criteria. The nurse and physician most closely involved in the care of the deceased patient will be asked to fill in a questionnaire within one week of the death. Six weeks after the death the researcher will send a questionnaire to a family carer, if they have given informed consent to being contacted by the researcher. In cases where the family carer does not respond to the questionnaire up to two reminders will be sent, two weeks after the initial sending of the questionnaire and two weeks later.

### Sample size calculation

The hypothesis of this cluster randomized trial is that there will be significant differences in symptom frequency and symptom burden between patients dying in the intervention group and those dying in the control group. Symptom frequency and symptom burden will be measured using the EOLD-SM and the EOLD-CAD. Because our primary outcome is a reduction in symptom frequency and symptom burden during the last 48 hours of life, we consider a total EOLD-CAD score of 3.2 (7.6%) as the minimum clinically important difference for implementing the Care Programme for the Last Days of Life [30]. A minimum increase of 3.2 in the intervention group compared to the control group corresponds with an effect size (EC) of about 0.55. A minimum change of 5% to 10% has been found to be clinically significant for symptom and quality-of-life analyses [31]. In order to calculate the sample size of this cluster trial two other elements are essential: the intra-cluster correlation coefficient and the average size of the cluster (number of cluster deaths). We estimate an intra-cluster correlation coefficient of between 0.02 and 0.05 [32] and a conservative average of 30 deaths per hospital per year based on observed mortality statistics, taking into consideration the non-included deceased patients. In Table 3 four ICC scenarios (from 0.02 to 0.05) intersect with three scenarios of average size of the cluster (from 20 to 40). This table reports different sample size scenarios necessary to detect an ES of 0.55 with alpha = 0.05 and a power of 80% conditional on the hypothesized levels of ICC (from 0.02 to 0.05) and average size of cluster (from 20 to 40).

**Table 3 Tab3:** **Total number of clusters required according to different average sizes of the clusters and ICC (ES = 0.55, alpha = 0.05, power = 0.80)**

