		**Average size of the clusters**		
		20	30	40
**ICC**	0.02	10	8	8
	0.03	12	10	10
	0.04	12	10	10
	0.05	14	*12*	10

A sample size of six clusters per group with 30 individuals per cluster achieves 80% power to detect a difference of 3.2 between the group means when the intracluster correlation is 0.05 using a Two-Sided *T*-test with a significance level of 0.05.

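### The stated 80% power assumes 30 records per hospital and allows nothing for family carer non-consent or non-return, so it is unsupported for the two carer-rated primary outcomes

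*Protocol article*

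**What the plan says.** The section on sample size calculation takes cluster size to be the number of deaths per cluster and sets it at "a conservative average of 30 deaths per hospital per year based on observed mortality statistics". The only deduction it mentions is for deceased patients who are not included. The difference of 3.2 on EOLD-CAD "corresponds with an effect size (EC) of about 0.55". The sentence under Table 3 concludes: "A sample size of six clusters per group with 30 individuals per cluster achieves 80% power to detect a difference of 3.2", at an ICC of 0.05. No rater is named. The planning range for the ICC is 0.02 to 0.05. The recruitment section asks for 10 to 12 hospitals, and the abstract says ten.

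Table 2 stars EOLD-SM and EOLD-CAD as "primary outcome" in both the nurse rows and the family carer rows.

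The two sets of records are collected differently:
- **Nurse.** Asked to complete the form within one week of the death. If the nurse refuses, the form passes to a colleague (sections on data collection and informed consent).
- **Family carer.** Asked for consent to contact shortly after the death, or by a posted form two weeks later. Then: "Six weeks after the death the researcher will send a questionnaire to a family carer, if they have given informed consent". Up to two reminders follow. No expected consent or response rate is given.

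**The concern.** One cluster size is used for two sets of records that will not be the same size. Thirty included deaths may come close to 30 nurse forms, because the form is handed on after a refusal. They yield 30 carer forms only if every carer consents and every questionnaire comes back, and planning for reminders shows that the authors do not expect that.

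Two of the four starred rater-by-scale outcomes therefore share a power statement whose cluster size they are unlikely to reach. If the nurse ratings favoured the programme and the carer ratings did not, a reader relying on the stated 80% would give the null carer result more weight than its actual sample supports.

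**Working it through.** **Inputs from the protocol article.** ES 0.55; two-sided alpha 0.05; ICC 0.02 to 0.05; m = 30 records per hospital; k = 6 hospitals per arm (12 in all), or k = 5 for the abstract's ten.

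**Assumptions.** The carer return is not stated, so m is varied. The same ES and ICC are taken to hold for carer ratings.

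**Method.**
- Design effect: DE = 1 + (m − 1) × ICC
- Effective number per arm: n = k × m / DE
- Non-centrality: δ = ES × √(n/2)
- Power from the non-central t with 2(k − 1) degrees of freedom

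**Step 1: reproduce the plan.** The smallest k giving at least 80% matches all 12 cells of Table 3. For the cell behind the power statement (k = 6, m = 30, ICC 0.05):
- DE = 1 + 29 × 0.05 = 2.45
- n = 180 / 2.45 = 73.5
- δ = 0.55 × √36.7 = 3.33
- with 10 df, power = 85.1%

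Five hospitals per arm give 76.0%, so the stated 80% means at least 80%, and rounding up to six leaves some slack.

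**Step 2: reduce m for carer returns, ICC 0.05.**

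| Returns per hospital | Share of 30 | DE | 12 hospitals | 10 hospitals |
|---|---|---|---|---|
| 30 | 100% | 2.45 | 85.1% | 76.0% |
| 24 | 80% | 2.15 | 81.8% | 72.1% |
| 20 | 67% | 1.95 | 78.5% | 68.5% |
| 18 | 60% | 1.85 | 76.4% | 66.3% |
| 15 | 50% | 1.70 | 72.3% | 62.1% |

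**Step 3: returns per hospital needed for 80%.**

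| ICC | 12 hospitals | 10 hospitals |
|---|---|---|
| 0.02 | 13.3 (44%) | 18.3 (61%) |
| 0.03 | 15.2 (51%) | 22.2 (74%) |
| 0.04 | 17.9 (60%) | 28.4 (95%) |
| 0.05 | 21.7 (72%) | 39.9 (out of reach with 30) |

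**Step 4: compare with Table 3.** Its column for 20 per cluster asks for 10, 12, 12 and 14 hospitals at ICC 0.02, 0.03, 0.04 and 0.05. Twelve hospitals meet the first three, and ten hospitals meet only the first.

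Pair matching, which may cost degrees of freedom, and adjustment for the baseline year, which may raise power, are not modelled. The plan's own calculation includes neither.

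**The case against.** A reader might infer that the carer-rated outcomes do not reach 80%, or that the design cannot give it. The article does not support that. It states no carer consent or response rate, so any shortfall depends on an assumed one. At 12 hospitals and ICC 0.05 the slack from rounding up absorbs a loss of about 28% of carers, and at lower ICCs about half may be lost. Table 3 also has a column for 20 per cluster, and three of its four entries fall within the planned 10 to 12 hospitals. These points stand, and they make the finding conditional.

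The low figures for ten hospitals at ICC 0.05 might also be read as the result of carer loss. Part of that shortfall is not: power is already 76.0% with all 30 records, because there are ten hospitals rather than 12, and this applies equally to the nurse ratings.

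It can further be said that the power sentence is conditional on its cluster size ("with 30 individuals per cluster achieves 80% power"), names no rater, and concerns a difference on EOLD-CAD. That is so, and nothing in it is miscalculated. But Table 2 makes the carer ratings primary, and no other power figure is offered for them. Nor is the column for 20 per cluster linked to carer loss.

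**Conclusion.** The point holds as an unstated planning assumption. The arithmetic of Table 3 is right. What is missing is any allowance for carer non-consent and non-return, so the 80% is unsupported for carer-rated EOLD-SM and EOLD-CAD. Whether those outcomes actually fall short depends on three things:
- **Return rate.** At 12 hospitals and ICC 0.05, power falls below 80% under about 22 returns of 30.
- **ICC.** At 0.02, 0.03 and 0.04, about 13, 15 and 18 returns suffice with 12 hospitals.
- **Number of hospitals.** With ten, about 18, 22 and 28 returns are needed at those ICCs. At 0.05, 80% is not reached even without carer loss, for either rater.

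All of this assumes that ES 0.55 and the stated ICC range carry over to carer ratings.

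**What to change.** In the section on sample size calculation, including the sentence under Table 3, state that the calculation with 30 per hospital applies to the nurse-rated outcome. Then give a separate power figure for the carer-rated outcomes at the number of hospitals actually taking part, using the carer return rate seen in the baseline year. If that rate cannot be used, show a range of returns across ICC 0.02 to 0.05, as in the tables above. If ten hospitals take part, restate the nurse-rated power at that number too.

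The cost is a few sentences and one recalculation, with no extra patients. Deaths are included from October 2012 and the baseline lasts one year, so by the article's publication in February 2015 the baseline return rate should be obtainable, although the article does not report it. The downside is a less favourable stated power for the carer ratings. Both raters' outcomes can stay primary: moving declared primary outcomes to secondary this late would be a substantive change and is not needed to correct the statement.

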**Flowchart of the cluster randomized controlled trial.**

### Study population

The inclusion criteria of the hospitals in the trial are:○ the cluster or hospital has one or more acute geriatric wards○ the medical and nursing head of one or more acute geriatric wards per hospital give consent for participation in the study

The inclusion criteria of patients are:○ those dying in the acute geriatric ward between October 2012 and March 2015○ those that having been hospitalized for more than 48 hours○ those having given informed consent at admission for the use of their personal information from medical or nursing records for the purposes of the study.

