### Recruitment of hospitals

Based on the cluster size calculation, 10 to 12 hospitals with one or more acute geriatric wards must be recruited. In order to recruit these hospitals, the study has been presented at three geriatric meetings. Shortly after these meetings information letters were sent to geriatricians. Geriatricians who were interested in participating were contacted by the researcher to make an appointment to explain and discuss the study and to sign an agreement of participation form. If geriatricians did not spontaneously contact the researcher, the researcher took the initiative herself to contact the geriatricians by phone about their interest and possible participation.

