### Randomization

At the end of the baseline assessment the included hospitals with one or more participating acute geriatric wards will be randomly assigned to the intervention group (implementing the Care Programme for the Last Days of Life) or to the control group (usual care).

As the number of clusters to be randomized is considerably smaller than in trials where the unit of randomization is the patient, there is a chance of baseline imbalance between the randomized groups. The risk of baseline differences can be reduced using pair-matched randomization [33]. Hospitals will be matched in comparable pairs in terms of 1) the number of deaths per year for the participating geriatric wards, and 2) the motivation of the participating wards in terms of the number of patients from whom they will acquire informed consent for participation in the baseline measurement period. Information related to the number of deaths and motivation per hospital will be sent to a statistician outside the research group, who will then match the pairs and randomize the hospitals into the experimental and control group using a random number generator.

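### Table 3 assumes equal hospital sizes although hospitals are expected to differ, so its tightest ten-hospital cells fall slightly short of 80% power (minor)

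*Protocol article*

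**What the plan says.** The sample size section of the protocol article plans for a standardised effect: "A minimum increase of 3.2 in the intervention group compared to the control group corresponds with an effect size (EC) of about 0.55". Its scenarios are those "necessary to detect an ES of 0.55 with alpha = 0.05 and a power of 80"%, for an ICC of 0.02 to 0.05 and an average of 20, 30 or 40 deaths per hospital. The planning value is 30 per hospital per year.

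The result is Table 3, "Total number of clusters required according to different average sizes of the clusters and ICC". The text below it gives one worked case, at ICC 0.05: "A sample size of six clusters per group with 30 individuals per cluster achieves 80% power", "using a Two-Sided *T*-test with a significance level of 0.05". The recruitment section then concludes: "Based on the cluster size calculation, 10 to 12 hospitals with one or more acute geriatric wards must be recruited". The abstract plans on ten.

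Elsewhere the article treats hospital size as variable. The inclusion criterion is that "the cluster or hospital has one or more acute geriatric wards". The Randomization section matches hospitals on "the number of deaths per year for the participating geriatric wards" and on the number of patients from whom the wards obtain consent.

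**The concern.** A table indexed by average cluster size reads as if it applied to hospitals whose sizes scatter around that average. If it was computed for identical sizes, its numbers are optimistic, because at a fixed average unequal sizes always lower power.

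The recruitment target is drawn from this table. At the planning size of 30, ICC 0.04 is the highest ICC for which Table 3 accepts ten hospitals; at 0.05 it already asks for twelve. If the ICC 0.04 cell passes only because sizes were taken as equal, the lower end of the target loses part of its support.

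Matching does not remove the problem. It balances size between the arms but leaves hospitals within an arm unequal.

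**Working it through.** **Inputs from the article.** Effect size 0.55, two-sided alpha 0.05, target power 80%, ICC 0.02 to 0.05, average size m = 20, 30 or 40, equal allocation.

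**Assumption.** The CV of cluster size is not given, so results are shown over a range.

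**1. Reproducing Table 3.** With k hospitals per arm, power comes from the non-central t distribution with df = 2(k−1), ncp = 0.55·√(k·m/(2·DE)) and DE = 1+(m−1)·ICC. The smallest even total reaching 80% matches all twelve cells, with cell powers from 80.0% to 90.3%. A normal approximation or individual-level df gives too few clusters; paired df gives too many. The table is therefore an equal-size calculation.

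Cells with almost no slack:

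| ICC | m | Hospitals | DE | ncp | Power, equal sizes |
|---|---|---|---|---|---|
| 0.05 | 40 | 10 | 1+39×0.05 = 2.95 | 0.55·√(200/5.90) = 3.20 | 80.0% |
| 0.04 | 30 | 10 | 1+29×0.04 = 2.16 | 0.55·√(150/4.32) = 3.24 | 81.0% |
| 0.02 | 30 | 8 | 1+29×0.02 = 1.58 | 0.55·√(120/3.16) = 3.39 | 80.5% |

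**2. Allowing for unequal sizes.** Two formulas are used.

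- Multilevel analysis, as the article plans: divide the equal-size information by nothing but multiply it by the relative efficiency 1−CV²·L·(1−L), with L = m/(m+(1−ICC)/ICC).
- Standard formula, more pessimistic: DE = 1+((1+CV²)·m−1)·ICC.

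Example for ICC 0.04, m = 30, CV 0.5. Multilevel: L = 30/(30+24) = 0.556, efficiency 1−0.25×0.247 = 0.938, ncp = 3.24×√0.938 = 3.14, power 78.5%. Standard: DE = 1+(37.5−1)×0.04 = 2.46, ncp = 0.55·√(150/4.92) = 3.04, power 75.8%.

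Power, multilevel / standard:

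| Cell | CV 0.33 | CV 0.4 | CV 0.5 | Falls below 80% from CV |
|---|---|---|---|---|
| ICC 0.05, m 40, 10 hospitals | 79.1 / 77.2% | 78.6 / 75.9% | 77.8 / 73.7% | 0.07 / 0.04 |
| ICC 0.04, m 30, 10 hospitals | 79.9 / 78.7% | 79.4 / 77.6% | 78.5 / 75.8% | 0.32 / 0.22 |
| ICC 0.02, m 30, 8 hospitals | 79.5 / 78.9% | 79.0 / 78.2% | 78.2 / 77.0% | 0.24 / 0.19 |
| ICC 0.05, m 30, 12 hospitals | 84 / 83% | 84 / 82% | 83 / 80% | 0.74 / 0.49 |

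**3. Which CVs are plausible.** Random variation of a count alone gives CV = 1/√m: 1/√40 = 0.16 and 1/√30 = 0.18. At that level only ICC 0.05 with size 40 fails (79.8 / 79.4%); ICC 0.04 with size 30 keeps 80.6 / 80.3%. If half the hospitals were twice as large as the others, CV would be 0.33.

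**4. Direct check.** With sizes 15, 15, 30, 45 and 45 in each arm (mean 30, CV 0.45), each arm's information is Σ n/(1+(n−1)·ICC). Power for ten hospitals is 84.2%, 78.8% and 73.8% at ICC 0.03, 0.04 and 0.05, against 86.1%, 81.0% and 76.0% with equal sizes.

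**5. Ten hospitals at an average of 30 and lower ICC.** Under the standard formula at CV 0.5, power is 88.6% at ICC 0.02 and 82.1% at ICC 0.03. Both hold.

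**The case against.** Table 3 is correct under the equal-size design effect that it uses, so there is no arithmetic slip. The shortfall also depends on a CV that the article does not give, and count variation alone breaks only one cell, away from the planning size of 30. Under the planned multilevel analysis the deficits are small: at CV 0.33 the ICC 0.04, size 30 cell has 79.9%, well inside the uncertainty of an ICC stated only as 0.02 to 0.05. All of this stands, and it makes the point minor.

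Baseline adjustment is planned, and Table 3 takes no credit for it. As an illustration only: if adjustment removed 20% of the between-hospital variance at the cost of one df, the ICC 0.04, size 30 cell would have 81.8% at CV 0.33 and 79.3% at CV 0.5 under the standard formula. The article does not quantify this gain, so it can neither be relied on nor dismissed.

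It may also be said that a condensed article can leave a CV allowance to the full protocol. That carries less weight here, because the table, its inputs and the recruitment target drawn from it are all printed.

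Two stronger readings are tempting. A reader might infer that ten hospitals suffice only up to an ICC of about 0.03. The figures do not support that: at ICC 0.04 ten still reach 80% while the CV stays below about 0.2 to 0.3. A reader might also infer that the whole target of 10 to 12 is undermined. It is not: the twelve-hospital case has slack, and the eight-hospital cell does not bear on the target, since ten hospitals at ICC 0.02 and size 30 have 91% with equal sizes.

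**Conclusion.** The point holds as a minor one. That Table 3 rests on equal sizes is established by exact reproduction of every cell, and the direction of the effect is certain. Its size is modest: about 1 to 4 points in the three tight cells at CV 0.4.

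Two of those cells bear on the target. ICC 0.05 with size 40 is marginally short under any realistic variation. ICC 0.04 with size 30 is short only above a CV of about 0.32 (multilevel) or 0.22 (standard formula). The twelve-hospital statement is sound: 85% with equal sizes and 83% / about 80% at CV 0.5.

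The magnitudes assume a CV that the documents do not supply and leave out any gain from baseline adjustment.

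**What to change.** Recompute Table 3 with a formula for unequal cluster sizes. Take the CV of included deaths per hospital from the mortality statistics already used for planning, or from the baseline year, which ends before randomisation. State the CV and the formula beside the table.

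Then restate what ten hospitals support at an average of 30: 80% power at ICC 0.02 to 0.03 for a CV up to about 0.5, and at ICC 0.04 only if the CV stays below about 0.2 to 0.3. The twelve-hospital statement can remain.

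The cost is a short recalculation and slightly less favourable stated figures. No extra hospitals or patients are asked for.
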